The overall objective of this multisite RCT is to determine the effectiveness of a T-MD intervention compared to usual care (behavioral management) in military-aged civilians with complex mTBI (anxiety/mood, cognitive, migraine, ocular, vestibular, sleep, and autonomic domains). The study involves three primary aims: (1) compare using an RCT the effectiveness of T-MD (anxiety/mood, cognitive, migraine, ocular, vestibular, sleep, autonomic domains) intervention to usual care (behavioral management) on improving clinical profile-based outcomes including symptoms, impairments, return to activity (RTA), and healthcare utilization costs in 200 military-aged civilian patients with complex mTBI; (2) to compare changes in brain activation (i.e., CBF) as measured by fNIRS in the T-MD and usual care intervention groups; and (3) to correlate changes in symptoms and impairment with brain activation as measured by fNIRS. We will also explore factors (e.g., demographics, medical history, injury information) that may influence the efficacy of T-MD on NSI, PGIC, and RTA outcomes.

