### Statistical analysis plan

2.6.

All data quality monitoring and analysis will be overseen by the lead biostatistician. Distributions of baseline characteristics for participants will be compared between T-MD and usual care intervention groups to assess effectiveness of the randomization. Statistical or clinical differences will be adjusted for in secondary analyses. All analyses for treatment group comparisons will use an intention-to-treat approach and results will be reported using the CONSORT extension to non-pharmacological randomized trials. The primary outcomes for this study are NSI (Aims 1, 3), PGIC scores (Aim 1) and brain activation as measured by fNIRS (Aims 2, 3). The NSI and PGIC will be measured at baseline, 2 weeks, 4 weeks, and 3 months post randomization. Brain activation will be measured at baseline and 4 weeks. NSI and fNIRS will be treated as continuous and PGIC scores will be dichotomized into minimal or no change vs. moderate or greater change. For Aim 1, we will analyze the NSI score using linear mixed models with fixed effects for site, intervention, time, and the intervention by time interaction along with a random effect for subject to control for the correlation within person over time. We will use a generalized linear mixed model with a logit link and the same fixed and random effects for the dichotomized PGIC outcome. We will test each intervention’s effect over time using the intervention*time interaction. For Aim 2, we will calculate change scores by subtracting the fNIRS value at 4 weeks from the baseline value. We will use a two-sample t-test to compare the change scores between the intervention and control group. For Aim 3, we will calculate change scores by subtracting the NSI value at 4 weeks from the baseline value. The efficacy of the intervention will be determined based on the results for each outcome and interpreted within the domain of that specific outcome with no adjustment for multiplicity. Pearson correlation will be used to examine the relationship of change in NSI to the fMRI value at 4 weeks in the intervention group.

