We also plan to explore factors (e.g., demographics, medical history, injury information, other symptoms, and impairments) that may influence the efficacy of T-MD on the outcomes of NSI, PGIC, and RTA. This will be done by focusing only on the 4-week time point and estimating within levels of each factor the intervention effect and 95% confidence intervals. We will also explore the independent effects of each treatment domain (e.g., anxiety/mood, cognitive, migraine, ocular, vestibular, sleep, autonomic) on primary and secondary clinical outcomes within the T-MD group using a mixed model with fixed effects for domain, time, and site along with a random effect for subject to control for the correlation within person over time. We will test each treatment domain’s effect over time using a domain*time interaction.

Calculations of sample size were based on the primary NSI primary outcome. We propose to randomize a total of 250 participants (125 in each intervention group) to allow approximately 200 participants for a complete case analysis at 4 weeks (assuming 20% attrition). With α = 0.05, two-tailed test, a sample size of 200 (*n* = 100 in each main effect group) will provide 80% power to detect a difference as small as 5 points on the NSI scale (standard deviation of 14) between the T-MD and usual care intervention groups assuming an autocorrelation of 0.7 for a 2 group repeated measures design with 4 repeated measures and AR (1) covariance structure. This sample size provides 99% power for the dichotomized PGIC (Aim 1) assuming 75% of the T-MD group and 50% of the control group reach moderate improvement and the same repeated measures design. Group sizes of 100 achieves 94% power to detect an effect size of 0.5 in fNIRS change using an independent samples, two-sided t-test (Aim 2, α = 0.05). For Aim 3, *n* = 100 in the intervention group provides 99% power to detect a Pearson correlation as small as 0.4. All power analyses were conducted in NCSS/PASS.

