### Limitations and future considerations

3.3.

The current sample will likely include more women than men, which does not accurately reflect the US active-duty military population, thereby limiting the generalizability of the findings to this population. Some participants may be more or less compliant with the assigned interventions, which could limit their effect. However, we will be conducting intention to treat analyses and assessing compliance *via* text-based survey to allow for a post-hoc evaluation of the effect of treatment compliance. Some participants might engage in additional interventions outside of those assigned in the treatment arms. Although we will be assessing these adjunct treatments *via* patient self-report, we will not be able to limit or assess the effects of these interventions. Although clinical care that occurs outside of the participating health systems is rare, CPT codes for this potential occurrence will not be available to the research team and therefore not be included in the healthcare utilization analysis. Many participants will be adjudicated with multiple clinical profiles and will receive a concomitant number of concurrent targeted treatments. As such, we will not be able to connect a specific intervention with a specific treatment effect *per se*. We are also assessing compliance *via* text messaging with at-home programs that are matched to the assigned profiles and this compliance does not include measures of intensity or duration for these at home exercises (i.e., RPE), and we also acknowledge limitation of reporting bias for these self-report compliance data. Moreover, efforts will be made to keep in-clinic contact time (i.e., time and attention from clinicians) equal for the two groups. However, the time spent on completing at home interventions, as part of the assigned profile, will vary between groups due to the inherent differences between these specific interventions for the treatment group and the general recommendations for behavioral regulation assigned to the control group. In addition, the results of this trial will inform the clinical care for symptoms and impairments commonly underlie the concussion clinical profiles (e.g., headache, mood, dizziness) and may not be generalizable to other less frequent symptoms and impairments that may also occur following concussion (e.g., tinnitus, stuttering). Researchers should also consider comparing the effect of concurrent treatments for multiple profiles to prioritized treatments (i.e., for a primary profile) to better delineate and capture intervention-specific effects. Finally, although we are powered to detect group changes across time in the primary outcomes, we are not powered to detect intervention and profile (i.e., domain) specific effects across participants.

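### The exploratory moderator analysis estimates the T-MD effect within each factor level but plans no contrast between levels, so it does not directly estimate whether the effect differs

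*Protocol article*

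**What the plan says.** The Introduction (section 1) announces, after the three primary aims, an exploration of "factors (e.g., demographics, medical history, injury information) that may influence the efficacy of T-MD on NSI, PGIC, and RTA outcomes". Section 2.6 repeats the purpose, widens the candidate list to "demographics, medical history, injury information, other symptoms, and impairments", and then fixes the method, restricted to the 4-week visit: "estimating within levels of each factor the intervention effect and 95% confidence intervals".

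Two interaction tests are named in section 2.6, and both answer other questions. For Aim 1: "We will test each intervention’s effect over time using the intervention*time interaction". For the treatment domains, within the T-MD arm only: "We will test each treatment domain’s effect over time using a domain*time interaction". Neither contains a term for a patient factor crossed with randomized arm, and no such term or contrast appears elsewhere in the article.

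**The concern.** The question is whether a factor changes the T-MD effect, so the quantity of interest is the effect in one level minus the effect in the other. The stated method gives the two effects and their intervals and stops there. It describes each level, but supplies no estimate or interval for the difference.

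Without that contrast, a reader has to judge moderation by eye from level-specific intervals. A common way to do this is to note that one interval excludes zero and the other does not. Each level has fewer participants than the whole trial and so less power, and that pattern can then arise easily when the true effect is the same in both levels. At stake are unsupported statements about which patients benefit from T-MD.

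This is not a detail left to an unseen analysis plan. The article names the question and states how it will be answered.

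**Working it through.** **Inputs from section 2.6.** Two-sided alpha 0.05; NSI difference 5 points; SD 14; 200 analysed, 100 per arm; AR(1) correlation 0.7 with 4 measures; PGIC 75% versus 50%.

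**Assumptions not in the documents.** A two-level factor split the same way in both arms; the same true effect in both levels; splits from 50/50 to 80/20. The article gives neither the number of factors nor their splits.

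**The plan's own figure.** The stated 80% power for NSI is reproduced by a 3-df Wald test of intervention by time with arm differences (0, 5, 5, 5) and the stated AR(1) structure: 80.6%. The inputs are therefore used as the plan intends. A comparison at a single time point, which is the setting of the moderator analysis, has 71.4% power without baseline adjustment. The article gives no figure for the moderator analysis itself.

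**Within-level power, even split (50 per arm per level).**
- SE = 14 × √(2/50) = 2.80.
- Power = Φ(5/2.80 − 1.96) = Φ(−0.174) = 43.1%.

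**Chance that exactly one level's interval excludes zero**, p1(1 − p2) + p2(1 − p1):

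| Split (per arm) | p1 | p2 | Exactly one |
|---|---|---|---|
| 50/50 | 0.431 | 0.431 | 49% |
| 60/40 | 0.498 | 0.358 | 50% |
| 70/30 | 0.561 | 0.282 | 53% |
| 80/20 | 0.617 | 0.203 | 57% |

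A simulation of 200,000 trials at the even split gave 49.1%.

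**Sensitivity.**
- With the 4-week NSI adjusted for baseline (baseline correlation 0.49 to 0.7) and the same splits: 42% to 62%.
- PGIC at 75% versus 50% in every level: 38% at 50/50 (power 0.740 in each level) to 49% at 70/30 (0.872 and 0.517).
- No true effect in either level: 2 × 0.05 × 0.95 = 9.5%.

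**Direct contrast, even split, NSI.**
- SE = √(2.80² + 2.80²) = 3.96 points; 95% CI half-width 1.96 × 3.96 = 7.8 points.
- False indication of moderation 5% per factor (simulated 5.0%), whatever the size of the uniform effect.
- Difference in effects detectable at 80% power: 2.80 × 3.96 ≈ 11.1 points. Power for a 5-point difference in effects: Φ(5/3.96 − 1.96) ≈ 24%.

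**Alternative reading: moderation only if the two intervals do not overlap.** The estimates must then differ by more than 2 × 1.96 × 2.80 = 10.98 points.
- Under a uniform effect this happens with probability 2 × Φ(−10.98/3.96) = 2 × Φ(−2.77) ≈ 0.6%.
- For a true difference of 11.1 points it happens about 51% of the time, Φ((11.1 − 10.98)/3.96), where the interaction test has 80% power.

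The same planned output therefore carries a false-indication rate of about 0.6% or about 50%, depending on a reading rule that the article does not state.

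**The case against.** The strongest reply is that the article promises estimation, not a decision. It says that factors will be explored, gives intervals rather than p-values, and nowhere says that a significant level beside a non-significant one will be called moderation. That stands. A reader might infer that the plan itself will declare moderation about half the time; the text does not support this. The 49% to 57% belongs to one way of reading the output, under an assumed uniform 5-point effect.

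It is also true that level-specific estimates with intervals are legitimate description, and that a contrast can be worked out from them because the levels hold different participants. So the method does not make a comparison impossible. What remains is that no comparison is planned, although comparison is the stated purpose.

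Three further inferences go too far.
- A reader might compound the risk over 5 or 10 factors. The article does not give the number, so no such total is claimed here.
- A reader might link false moderators to the practice guidelines listed as a deliverable in sections 3 and 3.4. Neither section ties the guidelines to this analysis.
- A reader might take the power caveat in section 3.3, "we are not powered to detect intervention and profile (i.e., domain) specific effects across participants", as already covering the point or as evidence for it. It concerns treatment domains and profiles, not patient factors crossed with arm.

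Finally, interaction tests also accumulate false positives over many factors and have little power here. Both are true. They are reasons to show the interaction interval and call it exploratory, not reasons to omit it.

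**Conclusion.** The concern holds in a limited form. The article asks which factors influence T-MD efficacy and fixes a method that does not directly estimate the difference in effect between levels. If intervals are read by whether each excludes zero, one factor with no moderating role would suggest moderation about 49% to 57% of the time for NSI (uniform 5-point effect, SD 14, 100 analysed per arm, splits 50/50 to 80/20). The corresponding figures are about 38% to 49% for PGIC (splits 50/50 to 70/30) and about 9.5% with no treatment effect. An interaction test holds the rate at 5%. Read by non-overlap alone, the rate is about 0.6%, at a heavy cost in sensitivity.

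Severity is low to moderate: the analysis is exploratory, and no primary aim or conclusion depends on it.

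**What to change.** For each factor, add an intervention-by-factor term to the 4-week analysis of each outcome: a linear model for NSI, and logistic models for dichotomized PGIC and for RTA status at 4 weeks. RTA needs its model named here because section 2.6 gives none for it. Report the interaction estimate with its 95% CI (a difference in points for NSI, a ratio of odds ratios for the binary outcomes) and state that any remark on moderation rests on that estimate. Keep the within-level effects and intervals beside it as description.

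Add one sentence saying that the analysis is exploratory and has low power: for an evenly split factor, an SE of about 4.0 NSI points and about 11 points detectable at 80% power. Uneven splits do worse.

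The cost is a change of wording, with no new data, visits or participants. The only downside is that the interaction intervals will be wide, which reports fairly how little the trial can say about moderators.

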#### Interventions for adjudicated concussion clinical profiles and usual care groups

2.4.4.

Participants assigned to the T-MD Intervention Group will be prescribed one or more of the intervention domains described in the following sections based on the results of the adjudication process. For example, one participant may be prescribed interventions for anxiety/mood, ocular, and vestibular domains, whereas another participant may be prescribed interventions for anxiety/mood, sleep, and autonomic domains. Each prescribed intervention will be tailored to the specific affected domains and sub-domains, based on clinical consensus (5). For example, within vestibular interventions, one participant may be prescribed only dynamic balance interventions, whereas another participant may be prescribed dynamic gait, gaze stability, and dynamic balance interventions. We will track the specifics of each participant’s intervention to evaluate individual intervention effects. T-MD interventions will be prescribed for a 4-week treatment period (See Description of TMD Interventions document presented in Supplemental material). The participants in the usual care intervention group will be prescribed standardized behavioral management strategies related to activity, sleep, hydration, nutrition, and stress (See Description of Behavioral Regulation Strategies document in Supplemental material).

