After the initial clinical evaluation and randomization into treatment or usual care groups, the clinical research team will adjudicate each participant’s complex mTBI diagnosis. Participant symptoms, impairments, and clinical exam/interview findings will be discussed to substantiate the presence of symptoms/impairments in each of the complex mTBI domains. An adjudication checklist will be completed during this process along with additional information from the clinical exam and interview. At the conclusion of the review and discussion, group consensus will be used to confirm each participant’s complex mTBI profiles and the final clinician-adjudicated and assessment-identified complex mTBI domains will be used to inform the targeted interventions for participants assigned to the T-MD group. At any point during the 4-week intervention of the study, domains can be updated and changed by treating clinicians. The adjudication process is based on the process developed in our TEAM-TBI work (22). A timeline of the study procedures and assessments is summarized in Figure 1. We will also tabulate each participant’s healthcare utilization and related costs using EHR at the conclusion of participation in the study protocol. We will also determine if participants are recovered (i.e., medically cleared for full return to activity) at 4 weeks and 3 months post-intervention.

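### The T-MD-only domain model cannot separate a domain intervention's effect from the natural course of the impairment, so it does not support domain-specific treatment effects

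*Protocol article*

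**What the plan says.** Section 2.6 announces the analysis in these words: "We will also explore the independent effects of each treatment domain". It is to be run "on primary and secondary clinical outcomes within the T-MD group using a mixed model with fixed effects for domain, time, and site", with a random subject effect, and each domain is tested for its "effect over time using a domain*time interaction". No usual-care participant enters the model.

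Treatment inside that arm follows the domain. Under section 2.4.4, T-MD participants "will be prescribed one or more of the intervention domains described in the following sections based on the results of the adjudication process". Section 2.5 says the "clinician-adjudicated and assessment-identified complex mTBI domains will be used to inform the targeted interventions for participants assigned to the T-MD group". The Introduction likewise ties each intervention to one affected domain. Section 2.4.4 adds that each participant's interventions will be tracked so that the effects of individual interventions can be evaluated.

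Section 3.3 points the other way. Because many participants will have several profiles and concurrent treatments, "we will not be able to connect a specific intervention with a specific treatment effect". It also says that the trial is not powered for domain-specific effects.

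**The concern.** A domain-by-time term fitted only in the T-MD arm compares treated people who have an impairment with people who do not have it. They differ in the intervention received and also in the condition that led to it. Nothing in the comparison is randomised, and a larger sample would not help, because no one in the model has the domain and goes without its intervention by design.

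Regression to the mean adds to the problem. Table 1 defines several domains by thresholds on instruments that Table 2 also lists as secondary outcomes (BSI-18, ImPACT, HIT-6, PSQI, mBESS, CP-Screen). Participants who are positive for a domain may therefore improve on its own measure with no intervention at all.

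At stake is how the domain results are read. The Introduction faults earlier multi-treatment studies for not considering separate effects of each intervention, so this analysis is part of what the trial offers as new. If its output is presented as an effect of each treatment domain, an intervention could be credited or discredited for the course of the impairment it was matched to.

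**Working it through.** **What the two designs identify.** Let A = 1 for T-MD and D = 1 if the domain is present. Write the expected 4-week NSI change as μ + αA + πD + τAD. Here π is the natural-course difference between people with and without the domain, and τ is the extra T-MD effect in those who have it.

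- T-MD arm only: (μ + α + π + τ) − (μ + α) = π + τ.
- Usual-care arm only: (μ + π) − μ = π.
- Difference between the two: τ.

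The stated model returns π + τ. The usual-care arm, which supplies π, is left out.

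**Inputs.** The plan gives no figure for this analysis, so there is none to reproduce. From the NSI sample-size text (2.6): SD 14, AR(1) autocorrelation 0.7, 100 analysed per arm. Four weeks is two visits after baseline, so the correlation is 0.7² = 0.49. Assumed here: 50% domain prevalence, seven independent domains, and the sizes of π and τ. The documents give none of these.

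**One contrast by formula, τ = 0.**

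- SD of change = 14 × √(2 × (1 − 0.49)) = 14.14.
- SE for 50 versus 50 = 14.14 × √(2/50) = 2.83.
- π = 5: 5/2.83 = 1.77, so two-sided power is about 42%.
- π = 8: 8/2.83 = 2.83, so power is about 81%.

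These are rates for a single 4-week change contrast, not for the full repeated-measures interaction test.

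**Simulation.** 3,000 replicates, 100 per arm, all seven domain indicators fitted, and τ and π attached to one domain. Negative values mean more improvement; the percentage is how often p < 0.05.

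| τ | π | T-MD-only coefficient | Two-arm arm-by-domain estimate |
|---|---|---|---|
| 0 | 0 | 0.0 (6%) | −0.1 (5%) |
| 0 | +5 | +5.0 (40%) | −0.1 (4%) |
| 0 | −5 | −4.9 (38%) | 0.0 (5%) |
| −5 | +5 | −0.1 (5%) | −5.1 (24%) |
| −5 | 0 | −5.0 (39%) | −5.0 (23%) |
| −5 | −5 | −10.0 (92%) | −5.0 (23%) |

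The T-MD-only column tracks π + τ throughout. A null intervention can look harmful or helpful, and a real benefit can vanish. The two-arm column tracks τ whatever π is, with low power.

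**Precision of the two-arm contrast.** With prevalence p, SE = SD × √(2/(100p) + 2/(100(1 − p))). The SD is 14.14 for change scores, or 14 × √(1 − 0.49²) = 12.20 with baseline adjustment. The difference detectable with 80% power is 2.80 × SE.

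- p = 0.5: SE 4.00 (change) or 3.45 (adjusted), so 11.2 or 9.7 points.
- p = 0.2: SE 5.00 or 4.31, so 14.0 or 12.1 points.
- T-MD versus usual care among domain-positive participants only, p = 0.5: 7.9 or 6.8 points.

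**The case against.** The strongest reply is that the analysis is exploratory, is not one of the three aims, and is disclaimed in section 3.3. That stands and it limits the severity. It does not remove the point. Section 3.3 rests on concurrent treatments and low power and does not mention that treatment and indication coincide. It also leaves the analysis in 2.6 and the promise in 2.4.4 unchanged. Exploratory status excuses imprecision, but not a label the estimate cannot carry.

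A second reply is that the preceding analysis in 2.6 may already hold the randomised comparison. It lists other symptoms and impairments among the factors for which T-MD is compared with usual care at 4 weeks, "estimating within levels of each factor the intervention effect and 95% confidence intervals". That is plausible, but the seven domains are not named there, and the T-MD-only model is still presented separately.

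A reader might also infer more than the text supports:

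- **That the coefficient is prognosis alone.** It is prognosis plus treatment effect.
- **That domain and treatment coincide perfectly.** Sub-domain tailoring, compliance and mid-course changes ("domains can be updated and changed by treating clinicians") loosen the link, although none of that variation is randomised.
- **That domain is entered as a single factor despite overlapping profiles.** The text speaks of each domain's effect, which fits seven yes/no indicators or seven models. The coding can be left to the SAP.
- **That the factor analysis is faulty because no interaction contrast is named.** It promises estimates with intervals and claims no test of modification, so that too is SAP detail.
- **That the promised practice guidelines rest on this model.** They are listed as a deliverable of the whole trial.

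**Conclusion.** The point holds. As stated, the domain-by-time term within the T-MD arm estimates natural course by impairment plus any treatment effect. It does not support the domain-effect label in 2.6 or the evaluation of individual interventions promised in 2.4.4, and both conflict with 3.3. This follows from how treatment is assigned and does not depend on any number.

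The rates of 38% to 42% at 5 points and 81% at 8 points only illustrate. They show how often an assumed natural-course difference would be declared significant at 50% prevalence, not how likely such a difference is.

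Severity is minor to moderate: the analysis is exploratory, section 3.3 concedes part of the problem, and no primary result is affected.

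**What to change.** 1. Estimate domain-specific effects in both arms with an arm-by-domain(-by-time) term, or as T-MD minus usual care at 4 weeks in those with and without each domain. Report estimates with 95% CIs as exploratory.
2. Take domain status from the Table 1 screening findings, which are collected before randomisation as part of eligibility. Do not use adjudicated or later-updated domains. Section 2.5 places adjudication after randomisation, and treating clinicians and research staff are unblinded (2.2). The Abstract places adjudication before randomisation, and the two accounts should be reconciled.
3. Relabel the T-MD-only model as descriptive recovery by profile.
4. Reconcile the wording of 2.4.4 and 2.6 with 3.3.

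The cost is plan wording and analysis code; no new data are needed, provided the full Table 1 screening is recorded for everyone. There are three downsides. Intervals will be wide: the detectable difference of about 10 to 11 NSI points at 50% prevalence is roughly twice the 5-point design difference. Screening domains may differ somewhat from adjudicated ones. And because profiles overlap, the contrast shows how the effect of the T-MD package differs by domain, not the isolated effect of one intervention, so the concurrent-treatment limitation in 3.3 remains.
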